## Methods/design

### Design

We will conduct a multi-site, single-blinded, randomized controlled trial involving at-home executive function training over a 12-week period. A total sample of 60 participants will be recruited at each testing site, comprised of 20 middle-aged adults (aged 45–60 years old) with normal hearing, 20 older-adults (aged 65–80 years old) with normal hearing, and 20 older-adults (aged 65–80 years old) with hearing impairment who use hearing aids (with a minimum of 6 months of experience using hearing aids). Participants will be randomized to either an executive function training group or a wait-list control group. The executive function training group will complete the home-based computerized cognitive training program during a 12-week period, while the wait-list control group will not complete any form of cognitive training during the 12 weeks. Participants in the wait-list control group will be offered the cognitive training program at the end of the study. Before and after the 12 week-period, participants in both groups will be asked to complete a series of cognitive, sensory, and mobility tests during two separate in-person sessions.

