### Inclusion criteria

To be enrolled in the study, participants must be aged 45–60 years old and have normal hearing, or 65–80 years old and have either normal hearing or bilateral hearing loss and use hearing aids (with a minimum of 6-months of experience using that set of hearing aids). Hearing ability will be assessed using pure-tone audiometry. An audiometric pure tone threshold average (PTA) will be calculated for each participant across 500 Hz, 1 kHz, 2 kHz, and 4 kHz. Participants will be included in the study if they have a PTA that is equal to or below 25 dB hearing level (HL) in the better ear for the normal-hearing middle-aged and older adults, and above 25 dB HL in both ears for the older adult hearing aid users [50]. While the grades of hearing loss have recently been updated [51], which categorize normal hearing as < 20 dB HL, we have opted to use the previous threshold of ≤ 25 dB HL for comparability with previous studies. All participants must be fluent English speakers and readers (i.e., monolingual or second language acquired early in life). Participants are also required to be physically present at Concordia University’s Loyola Campus in Notre-Dame-de-Grâce, Québec, Canada or the Toronto Rehabilitation Institute, University Centre in Toronto, Ontario, Canada, for a total of four in-person assessment sessions.

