### Data analysis

#### Planned analyses

All data analyses will be completed using IBM SPSS Statistical Software and/or R. Data will be screened and corrected for normality, outliers, and missing values. Descriptive statistics (e.g., means and standard deviations for continuous variables; frequencies and percentages for categorical variables) will be presented for the demographic and baseline characteristics. Chi square tests (for categorical variables) or One-Way ANOVAs (for continuous variables) will be used to determine if there are any differences between groups at baseline (i.e., middle-aged vs. older adults vs hearing aid users; training vs. control groups).

In order to evaluate our primary hypothesis (i.e., that executive function training will lead to greater improvements in dual-task performance compared to a wait-list control group), separate 3 × 2 × 2 Mixed Factorial ANOVAs will be conducted for each of the primary outcome measures (i.e., 2-back accuracy and reaction times, CRM accuracy, temporal gait parameters, posturography variables, DTC scores), whereby the Between-Subjects factors will include Age/Hearing Group (middle-aged, older adult, hearing aid users) and Training Group (cognitive training, control), the Within-Subject factor will include Time (pre- vs. post-evaluations), and Covariates will include sex and education. Observation of a statistically significant Time by Training Group interaction in any of the primary outcome measures will be considered preliminary evidence for training efficacy. In order to examine our second and third hypotheses (i.e., that largest improvements in dual-task performance and greatest augmentation of brain activity will be found in older hearing aid users, followed by normally-hearing older adults, and then middle-aged adults) separate One-Way ANOVAs will be used on the dual-task and HbO change scores within the cognitive training group, whereby the Between Subjects factor will include Age/Hearing Group (middle-aged, older adult, hearing aid users). Observation of a statistically significant main effect of Group will be followed up by post hoc pairwise analyses with Bonferroni corrections in order to determine whether our hypotheses are supported.

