Linear mixed effects models will also be fitted for each of our outcome measures, particularly if there is a large amount of missing data or if there is an unequal amount of variance across groups. Specifically, Fixed effects will include Age/Hearing Group (middle-aged, older adult, hearing aid users), Training Group (executive function training, control), Sex (male/female), and Time (Pre- vs. Post-Training), Random effects will include the individual participants, and Covariates will include education.

Lastly, in order to elucidate whether brain activity reflects neural compensation or inefficiency, correlations between dual-task performance and HbO levels will be conducted at baseline and after 12 weeks. All statistical tests will be two-tailed, and a *p*-value of less than 0.05 will be considered to indicate statistical significance. Effect sizes will be calculated using Hedges’ *g.*

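### The One-Way ANOVAs that compare training gains between hearing aid users and normal-hearing older adults do not adjust for age in years, although the contrast is not randomised and both groups span 65–80

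*Protocol article*

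**What the plan says.** All of the following is in the Protocol article.

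- **Mixed ANOVA for the primary hypothesis (Planned analyses).** "the Between-Subjects factors will include Age/Hearing Group (middle-aged, older adult, hearing aid users"), crossed with Training Group and Time. For adjustment, "Covariates will include sex and education". Efficacy is judged by the Time by Training Group interaction.
- **Hypotheses 2 and 3 (Planned analyses).** "separate One-Way ANOVAs will be used on the dual-task and HbO change scores within the cognitive training group", with Age/Hearing Group as the only factor. No covariate is listed. A significant group effect leads to Bonferroni-corrected pairwise comparisons.
- **Linear mixed model (Planned analyses).** Sex is a fixed effect, and "Random effects will include the individual participants, and Covariates will include education".
- **Eligibility (Inclusion criteria).** "participants must be aged 45–60 years old and have normal hearing, or 65–80 years old" and with normal hearing or with bilateral hearing loss and hearing aids. Age is therefore known for every participant.
- **Group size (Design).** Each site recruits 20 per group, for example "20 older-adults (aged 65–80 years old) with normal hearing".
- **Randomization.** Allocation to training or control is done within each of the three age/hearing groups, with equal arms.
- **Baseline tests (Planned analyses).** Differences between the age/hearing groups will be tested at baseline, but no consequence for the models is given.

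**The concern.** Hypothesis 2 predicts that hearing aid users gain more than normal-hearing older adults; hypothesis 3 makes the parallel prediction for brain activity. Nobody is randomised to a hearing group, so this is an observational contrast inside a randomised trial. The group factor separates middle-aged from older participants, but does nothing about an age difference between the two older groups, since both carry the same band.

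Such a difference is plausible. The Background gives a prevalence of bilateral hearing loss of up to two-thirds at age 70 and over, and the note to the study flowchart calls the hearing aid users' loss age-related. Selecting for normal hearing within 65–80 may therefore favour the younger part of the band. The trial's own hypotheses also suppose that age matters for gain, since normal-hearing older adults are expected to gain more than normal-hearing middle-aged adults. If gain rises with age and hearing aid users are older, the unadjusted comparison is biased towards hypothesis 2. If gain falls with age, a real hearing effect would be masked.

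**Working it through.** The plan states no figure on this point, so there is nothing to reproduce. The check has four parts.

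**1. Where age enters.**

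| Model | Age as a band | Age in years | Other adjustment |
|---|---|---|---|
| Mixed ANOVA | yes | no | sex, education |
| One-Way ANOVAs (hypotheses 2 and 3) | yes | no | none |
| Linear mixed model | yes | no | sex, education |

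Each band is 15 years wide (60 − 45 = 15; 80 − 65 = 15).

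**2. Size of the bias.** For an unadjusted contrast of two groups:

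bias (in SD of change) = r × (mean age gap / SD of age)

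where r is the correlation of age with the pre-to-post change. Assumptions: SD of age = 15/√12 = 4.33 years (ages uniform over a 15-year band), gap of 2–4 years, r of 0.2–0.4. None of these is in the protocol.

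- Low end: 0.2 × 2/4.33 = 0.09 SD
- Middle: 0.3 × 3/4.33 = 0.21 SD
- High end: 0.4 × 4/4.33 = 0.37 SD
- Wider range, 1–5 years and r of 0.1–0.4: 0.02 to 0.46 SD
- No gap, or r = 0: zero

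**3. Effect on the test.** With 20 per group per site and equal arms, about 10 per group are trained. The table gives two-sided false-positive rates from the noncentral t, 10 versus 10, 18 degrees of freedom, ignoring the preceding overall test.

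| Bias (SD) | at 0.05 | at 0.05/3 = 0.017 (Bonferroni) |
|---|---|---|
| 0.09 | 0.054 | 0.019 |
| 0.21 | 0.073 | 0.027 |
| 0.37 | 0.123 | 0.052 |

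**4. Price of adjusting.**

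- *Degrees of freedom.* With 30 trained participants in three groups, the error degrees of freedom fall from 27 to 26. Power goes from 0.195 to 0.194 at f = 0.25, and from 0.442 to 0.440 at f = 0.40 (both f assumed).
- *Variance of the older-group contrast.* With the age slope estimated from the two older groups alone, the factor is 1 + (gap/2)²/4.33². A gap of 2 years gives 1 + 1/18.75 = 1.05; a gap of 5 years gives 1 + 6.25/18.75 = 1.33. If the middle-aged group has the same age SD and shares a common slope, the factor is 1 + gap²/(6 × 18.75), that is 1.04 and 1.22, so 1.05–1.33 is the cautious range.

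**The case against.** **Age is already modelled.** One might infer that age is missing from every analysis. It is not: Age/Hearing Group is in all three models, and with uniform ages it explains about 83% of the variance of age. Only age within the band is absent. But that is the part in which the two older groups can differ.

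**The main efficacy test is randomised.** A reader might also conclude from the covariate list of the mixed ANOVA that the primary result is confounded. It is not. Time by Training Group compares arms randomised within each age/hearing group, so leaving out age can affect precision there but not validity.

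**The age gap is not in the documents.** This stands. The protocol gives no ages for the groups, and a prevalence at 70 and over does not show that this sample will differ. The gap is an assumption. The planned baseline tests could reveal one, but nothing is said to follow from them.

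**Change scores cancel level effects.** This stands too. If age affects performance equally before and after, it drops out of the change score and neither biases the contrast nor inflates its error. Only a relation of age to gain counts, so r must be read in that sense. The same limits any precision benefit: removing r² = 4–16% of residual variance applies only if age correlates 0.2–0.4 with change.

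**The SD is a convenience.** Two groups both uniform over 65–80 would have no gap. If 4.33 is instead the pooled SD, a 4-year gap implies a within-group SD of √(18.75 − 4) = 3.84 and a high-end bias of 0.4 × 4/3.84 = 0.42 SD. The order of magnitude is unchanged.

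**Bonferroni limits the damage.** It does: at the high end the pairwise false-positive rate is about 5% against a nominal 1.7%. The estimated difference remains biased by the same amount, and correction does nothing for an effect that is masked.

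**Conclusion.** The point holds for the One-Way ANOVAs of hypotheses 2 and 3, and for the contrast of hearing aid users with normal-hearing older adults in particular. The article fixes its covariate lists, so this is a stated choice and not a detail left for later. Under the assumed gap of 2–4 years, SD of 4.33 years and age-by-change correlation of 0.2–0.4, the bias is about 0.09–0.37 SD, in either direction according to the sign of the correlation; it is zero if either the gap or the correlation is absent. The documents make an age gap plausible but do not establish it, and they do not support any claim that the randomised comparison is confounded. This is a modest weakness in a non-randomised comparison, worth correcting because the variable is already collected.

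**What to change.** Replace the One-Way ANOVAs on the dual-task and HbO change scores by an ANCOVA with Age/Hearing Group and age in years, centred at the mean of the participant's age band (45–60 or 65–80). Do not centre at each hearing-group mean, as that would leave the age gap inside the hearing contrast. Raw age is also unsuitable for the overall group test: the bands do not overlap, and it would take out the age difference that the middle-aged versus older comparison is meant to show.

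The same term may be added to the mixed ANOVA and the linear mixed model. For Time by Training Group it serves precision only, and it needs the age-by-time term to do so, since an age effect on level alone does not touch pre-to-post change.

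Cost: a change of wording, no new data, one degree of freedom for age, and about 1.05 to 1.33 times the variance of the older-group contrast if the age gap is 2 to 5 years. Adding sex and education to the ANCOVA as well would use further degrees of freedom with about 30 trained participants per site, and is not needed for this point.

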**Discussion:**

This research will establish the efficacy of an at-home cognitive training program on complex auditory and motor functioning under laboratory and simulated real-world conditions. This will contribute to rehabilitation strategies in order to mitigate or prevent physical and cognitive decline in older adults with hearing loss.

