## Measures

### Primary outcome measures

The primary outcome measures will include tests of single- and dual-task cognitive, gait, and postural performance in a laboratory environment, including simulated realistic conditions. The outcome measures of interest will include cognitive accuracy and reaction times, temporal gait characteristics, posturography variables, and dual-task cost scores. The older hearing aid users will be required to wear their hearing aids during all testing procedures. Two sets of research assistants will be present at each testing site—one to work with the participant and provide instructions for the tasks, and the other to work with the technical apparatus and ensure that the data are being captured and recorded appropriately.

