### Auditory 2-back paradigm

*2-Back Task:* The same auditory 2-back task as the Concordia site [41] will be used; however, trials will last 60 s instead of 30 s in order to capture a sufficient amount of reliable posturography data [25]. The amplitude of the loudspeakers will be individually adjusted using an auditory 1-back task to ensure optimal audibility and comfort across participants. Specifically, participants will hear 15 untimed, single digits where they will have to repeat the digit they heard out loud to the researcher immediately after the digit is presented. In order to participate in the study, participants must attain at least 70% accuracy or higher. If the amplitude is uncomfortably loud, it will be reduced (ensuring at least 70% accuracy) and the amplitude will then be set at this level for the remainder of the experiment. Accuracy and reaction time will be measured using a handheld gaming controller (Forty4 Wireless Gaming Controller). During the main experimental task, participants will make a button press indicating whether the number they are currently hearing is the same or different than the number presented *n* steps previously (i.e., 1-step previously during the practice trials, or 2-steps previously for the 2-back task). During single-task conditions, the participants will complete the 2-back while sitting on a chair on top of the force plate within StreetLab at the same approximate eye height as standing.

*Postural Task.* Static balance will be measured by having participants stand with their feet shoulder-width apart on a force platform. In order to control for differences in hand positions across the single-task standing and dual-task trials (since participants use handheld joysticks during the 2-back task), participants will be required to hold the joystick in the same position as the dual-task trials (but will not need to make any button responses). In order to manipulate postural load, participants will complete the standing balance task with their eyes open and eyes closed. Postural measures will include spatial (centre of pressure path length; cm), temporal (velocity; cm/s) and variability (root means square, standard deviation) measures in the anterior–posterior (front and back) and medial–lateral (side-to-side) orientations.

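### Any one unadjusted p<0.05 among many unranked primary outcomes counts as preliminary evidence of efficacy, so the false-positive risk of that conclusion is far above 5%

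*Protocol article*

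**What the plan says.** Under Planned analyses, a separate mixed ANOVA (age/hearing group by training group by time) is run for each primary outcome. The outcomes are listed as "2-back accuracy and reaction times, CRM accuracy, temporal gait parameters, posturography variables, DTC scores". The decision rule follows: a "statistically significant Time by Training Group interaction in any of the primary outcome measures will be considered preliminary evidence for training efficacy". The threshold is common to all analyses: "All statistical tests will be two-tailed, and a *p*-value of less than 0.05 will be considered to indicate statistical significance". Bonferroni appears once, for pairwise comparisons of the age/hearing groups after a significant group effect (second and third hypotheses). It is not attached to the primary interactions.

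The section Primary outcome measures sets the breadth of the list: "The primary outcome measures will include tests of single- and dual-task cognitive, gait, and postural performance in a laboratory environment", with DTC scores added in the next sentence. No outcome is placed ahead of the others.

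The Abstract's Discussion says "This research will establish the efficacy of an at-home cognitive training program", and Research objectives and hypotheses makes this the primary objective.

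**The concern.** A rule that accepts any one of many tests at 0.05 has a false-positive rate that grows with the number of tests. Because the article states the rule outright, a statistical analysis plan could repair it only by overriding it.

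The rule also does not match its hypothesis. The primary hypothesis concerns dual-task performance, yet a single-task result would satisfy the rule. The article itself reports that older adults with hearing loss tend to protect posture or walking at the expense of the cognitive task. A shift of priority, with one task better and the other worse, could therefore meet the rule without any overall gain.

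At stake is the trial's only stated efficacy criterion. One nominally significant interaction out of a long list cannot carry a statement that efficacy has been established.

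**Working it through.** **The plan's own figure.** The article states no family-wise error rate. Its only error calculation is the sample size: 18 per group for power 0.95 at alpha 0.05, for one interaction on walking speed. For a two-arm, two-time interaction, lambda = f² × N × 2/(1 − r). With r = 0.5 (assumed) and 0.304 entered as Cohen's f, N = 36 gives lambda = 13.3 and power 0.943; N = 38 gives 0.954. The figure is thus approximately reproduced under that reading, as a design for a single test at 0.05. Walking speed cannot serve as an implied lead outcome: the treadmill speed is fixed for each participant, and the gait measures listed are step and stride times.

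**Counting the tests.** Assumptions: conditions are tested separately; every posture measure is split into anterior–posterior and medial–lateral; velocity and RMS are left out as likely duplicates of path length and SD.

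- Concordia, dual-task: 2-back accuracy and reaction time (2) + mean and variability of step and stride time (4) = 6. With single-task and DTC versions: 6 × 3 = 18.
- KITE, dual-task: 2-back accuracy and reaction time × 2 eye conditions (4) + path length and SD × 2 directions × 2 eye conditions (8) + CRM accuracy × 2 loads (2) + 4 posture scores × 2 loads (8) = 22.
- KITE with single-task and DTC: 12 + 24 + 6 + 4 × (1 single + 2 dual + 2 DTC) = 62. The CRM paradigm has only one single-task standing condition, hence the 5.

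The posture list reads "Postural measures will include spatial (centre of pressure path length; cm), temporal (velocity; cm/s) and variability (root means square, standard deviation) measures". Keeping velocity and RMS would give 38 and 106; those counts are not used here. The mixed models planned for the same outcomes are not counted either.

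**Chance of at least one p<0.05 under the null.** For independent tests it is 1 − 0.95^m. For a common correlation ρ between test statistics it is 1 − ∫ φ(t) [Φ((1.96 − √ρ t)/√(1−ρ)) − Φ((−1.96 − √ρ t)/√(1−ρ))]^m dt. The article gives no correlations, so a range is shown.

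| Tests | ρ = 0.7 | ρ = 0.5 | ρ = 0.3 | ρ = 0 |
|---|---|---|---|---|
| Concordia, 6 | 16.4% | 20.7% | 24.1% | 26.5% |
| Concordia, 18 | 27.7% | 39.8% | 50.9% | 60.3% |
| KITE, 22 | 30.1% | 43.9% | 56.9% | 67.6% |
| KITE, 62 | 43.3% | 67.2% | 85.7% | 95.8% |

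The zero-correlation ends for 18 and 62 are upper bounds, because each DTC is computed from the single- and dual-task scores also being tested.

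**Both sites.** The samples are separate, so the errors compound. For dual-task scores only (6 + 22):

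- ρ = 0.7: 1 − (1 − 0.164)(1 − 0.301) = 42%
- ρ = 0.5: 1 − (1 − 0.207)(1 − 0.439) = 56%
- ρ = 0: 1 − 0.95^28 = 76%

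**Only results favouring training.** Each test then has 0.025 in the relevant tail. From ρ = 0.7 to ρ = 0 the rates are 8–14% (6 tests), 15–43% (22 tests) and 22–51% for both sites. The last upper end is 1 − 0.975^28.

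**Stress check.** At ρ = 0.9 the two-sided rates are 10.8% (6) and 15.9% (22), or 1 − 0.892 × 0.841 = 25% for both sites.

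**The case against.** The best defence is that the article claims little: the rule yields only preliminary evidence, and a modest trial may screen many outcomes. That is a fair description of the rule's wording and should be kept when citing it. It does not settle the matter, because the objective is to establish efficacy and no stricter criterion is offered.

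Several stronger readings are tempting but unsupported.

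- **Dozens of tests at each site.** Concordia has 6 to 18; only KITE can reach dozens, and its number depends on whether conditions are pooled and whether the direction split applies to all posture measures. The article does not say.
- **A false claim is more likely than not.** This depends on the count and the correlation. It fails for the narrow trial-wide count at ρ = 0.7 (42%) and for six tests at Concordia throughout.
- **A near-certain error at KITE.** This would need 106 independent tests, which is impossible if some are duplicates and DTCs derive from other scores.
- **An effect favouring control would count as efficacy.** The rule names no direction, but the hypothesis in the same paragraph is greater improvement with training, so the direction is implied. This is an ambiguity to close.
- **Velocity and RMS are exact duplicates.** Velocity is one only if it is mean velocity over the fixed 60 s trial. RMS equals SD only if the trace is mean-centred, which is not stated.

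The priority-shift worry is also partly met: DTCs are calculated for both the motor and the cognitive task, so a trade-off would be visible. The rule still does not require anyone to look at the paired task.

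**Conclusion.** The concern stands as a defect in a stated rule. With no ranking and no adjustment of the primary interactions, the conclusion of preliminary efficacy carries a trial-wide false-positive risk of about 42 to 76%, even counting only dual-task scores without likely duplicates. If only training-favouring results count, it is 22 to 51%. Including single-task scores and DTCs raises the two-sided per-site figures to about 28–60% at Concordia and 43–96% at KITE, the upper ends being bounds.

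These figures rest on the counting assumptions above and on an assumed common correlation of 0 to 0.7. No combination examined comes near 5% trial-wide; even ρ = 0.9 gives 25% two-sided. The exact rate cannot be known from the article, but the conclusion does not depend on it.

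**What to change.** Before analysis, replace the any-outcome rule in the protocol, the analysis plan and the registry entry:

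1. Name one cognitive and one motor dual-task primary per site, each a single score with its paradigm and condition. At KITE this means choosing the 2-back or CRM paradigm and, for 2-back, a named eyes-open or eyes-closed condition or their average. Dual-task 2-back accuracy is one candidate because both sites measure it; the choice belongs to the trial team.
2. Apply Holm at two-sided 0.05 across all four tests over both sites if either site alone can support the claim. Running each site at 0.05 separately would leave 1 − 0.95² = 9.75%.
3. State that the effect must favour training, and report the paired task beside each primary result.
4. Label single-task scores, DTCs and all remaining variables secondary or exploratory.

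The cost is wording and a registry update; no participants or assessments are added, and the article says recruitment is still under way. The real price is that fewer outcomes can carry the claim and each faces a stricter level. Holm's first step is 0.05/4 = 0.0125. With the power formula above, N = 60 per site, r = 0.5 and no attrition, power for one test at 0.0125 instead of 0.05 falls from 0.996 to 0.98 if 0.304 is Cohen's f. If 0.304 is a true d (f = 0.152), it falls from 0.64 to 0.42.

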## Abstract

**Background:**

Hearing loss predicts cognitive decline and falls risk. It has been argued that degraded hearing makes listening effortful, causing competition for higher-level cognitive resources needed for secondary cognitive or motor tasks. Therefore, executive function training has the potential to improve cognitive performance, in turn improving mobility, especially when older adults with hearing loss are engaged in effortful listening. Moreover, research using mobile neuroimaging and ecologically valid measures of cognition and mobility in this population is limited. The objective of this research is to examine the effect of at-home cognitive training on dual-task performance using laboratory and simulated real-world conditions in normal-hearing adults and older hearing aid users. We hypothesize that executive function training will lead to greater improvements in cognitive-motor dual-task performance compared to a wait-list control group. We also hypothesize that executive function training will lead to the largest dual-task improvements in older hearing aid users, followed by normal-hearing older adults, and then middle-aged adults.

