### Research objectives and hypotheses

Given the association between hearing loss and cognitive and physical impairment, there is great value in identifying treatment strategies targeted at delaying or mitigating further decline. The primary objective of our research is to establish the efficacy of an at-home computerized executive function training program on complex auditory and motor functioning measured under both laboratory and simulated real-world conditions. Behavioural and neuroimaging data will be collected in middle-aged and older adults with normal hearing sensitivity thresholds, as well as older hearing aid users.

It is hypothesized that executive function training will lead to greater improvements in dual-task performance compared to no training (i.e., wait-list control group). Furthermore, it is hypothesized that the greatest improvements will be seen in older hearing aid users, followed by older adults with normal hearing, and then middle-aged adults. We also predict a differential pattern of neural plasticity as a function of age/hearing group following executive function training.

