Brain activity will be measured (Pre- and Post-Training) using functional near infrared spectroscopy (fNIRS) at Concordia’s PERFORM Centre. The working brain is in constant need of supply of glucose and oxygen for efficient functioning. As such, levels of oxygenated hemoglobin (HbO) and deoxygenated hemoglobin (HbR) in the brain can be used as neurobiological indicators of cortical activation. Increased brain activation leads to increased blood volume and blood flow, resulting in an increase in HbO and a decrease in HbR. Conversely, decreased brain activation leads to decreased blood volume and blood flow, resulting in a decrease in HbO and an increase in HbR. Functional near infrared spectroscopy provides a non-invasive measure of HbO and HbR fluctuations in the cerebral cortex with high temporal resolution [77]. A mobile (wireless/Bluetooth) fNIRS device will be used to allow participants to freely complete the experimental task while walking (Artinis Brite MKIII, Netherlands). Light optode placement will follow a 24-channel frontal template provided by the analysis software OxySoft (Version 3.3.30). Data pre-processing involving the visual inspection of motion artifacts, detection of bad channels, Modified Beer-Lambert Law (MBLL) conversion, and band pass filtering (0.005 Hz-0.1 Hz), will be conducted using MATLAB (Version R2021b) and the open-source application Brainstorm [78]. Additionally, all trials will be normalized to baseline, which will be taken during a quiet standing condition prior to each trial. A single HbO activation average will be computed for each participant for each trial type (i.e., single-task walking, single-task 2-back, and dual-task). HbO change scores will then be derived to compare Pre- and Post-Training cortical activation levels.

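### Hypotheses 2 and 3 are tested within the trained arm only, so a group difference in training effect cannot be separated from a group difference in retest gain or drift

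*Protocol article*

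**What the plan says.** Hypothesis 2 is worded as an effect of training. The abstract states: "We also hypothesize that executive function training will lead to the largest dual-task improvements in older hearing aid users". Research objectives and hypotheses repeats that "the greatest improvements will be seen in older hearing aid users, followed by older adults with normal hearing, and then middle-aged adults". Hypothesis 3, as given under Planned analyses, predicts the same ordering for the increase in brain activity.

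For hypothesis 1, Planned analyses uses a 3 x 2 x 2 mixed ANOVA that includes the wait-list controls. Its criterion is: "Observation of a statistically significant Time by Training Group interaction in any of the primary outcome measures".

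For hypotheses 2 and 3 the plan changes method: "separate One-Way ANOVAs will be used on the dual-task and HbO change scores within the cognitive training group". Age/hearing group is the only factor. The decision rule follows: "Observation of a statistically significant main effect of Group will be followed up by post hoc pairwise analyses with Bonferroni corrections", and these pairs determine whether the hypotheses are supported.

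For fNIRS, Secondary outcome measures says "HbO change scores will then be derived to compare Pre- and Post-Training cortical activation levels". HbO is not in the list of outcomes for the 3 x 2 x 2 ANOVA. Planned analyses also provides linear mixed models for each outcome measure, with training group and time among the fixed effects. It names no interaction there and does not tie those models to hypotheses 2 or 3.

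**The concern.** Whether training works better in one group than another is a question about trained-minus-control change, compared between groups. The planned test compares raw pre-post change between three groups that differ in age and hearing, with nothing to show how each would have changed untrained.

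Untrained change is plausible. Study procedure has all participants repeat the same assessments after 12 weeks, and Secondary outcome measures uses alternate RAVLT lists specifically to limit practice effects. If retest gain or drift differs by age or hearing, the difference enters the planned F test in full. It could produce the predicted pattern without any difference in training effect, or cancel a real one.

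At stake are two of the three stated hypotheses. The information needed is already planned: Waitlist control group says controls complete both assessments.

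**Working it through.** **Plan's own figure.** No sample size or power is given for hypotheses 2 or 3. The only calculation is 18 per group for Training Group x Time on walking speed, raised to 18/0.9 = 20 for attrition. The 18 cannot be uniquely reproduced, because the text does not say which effect size, pre-post correlation or number of groups was entered. Nothing below depends on it.

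**Inputs from the article.** There are 60 participants per site, 20 per age/hearing group (Design). Allocation is equal within each group (Randomization), so about 10 trained and 10 controls per group per site. Alpha is 0.05, two-tailed. fNIRS is measured at one site only, so 10 per cell is the relevant size for HbO.

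**Assumed inputs.** Change scores are normal with SD 1 in every cell. Retest gain is equally spaced over the three groups at 0, gap/2 and gap. The gap is not in the documents, so a range is shown.

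**What each test compares.** Let r_g be retest gain plus drift in group g, and t_g the training effect.

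- Planned test: differences between groups in r_g + t_g.
- Three-way interaction: differences between groups in (r_g + t_g) - r_g = t_g.

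**No training effect (all t_g = 0), 10 per cell.** The noncentrality of the planned F test on 2 and 27 degrees of freedom is λ = n Σ(μ_g - mean)² = n × gap²/2.

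- gap 0.25: λ = 10 × 0.0625/2 = 0.3125
- gap 0.5: λ = 10 × 0.25/2 = 1.25
- gap 1.0: λ = 10 × 1/2 = 5.0

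| Gap, SD of change | Planned omnibus significant | Hearing aid users above both others after Bonferroni pairs | Three-way interaction significant |
|---|---|---|---|
| 0 | 5% | – | 5% |
| 0.25 | 7% | about 0.5% | 5% |
| 0.5 | 14% | about 1.5% | 5% |
| 1.0 | 46% | about 7% | 5% |

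A weaker form of false support, a significant omnibus with hearing aid users above middle-aged adults only, occurs in about 9% of trials at a 0.5 SD gap and 39% at 1.0 SD. With 20 per cell, the omnibus rates for gaps of 0.25, 0.5 and 1.0 SD are about 10%, 26% and 79%; the interaction stays at about 5%.

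**Opposite direction.** A true training-effect gap of 0.8 SD, cancelled by a retest gap of -0.8 SD, is found in 5% of trials by the planned test and 18% by the interaction (10 per cell).

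**Cost in power.** Suppose the true training-effect gap is 1.0 SD and there is no retest gap. The planned test has λ = 5.0 and power 0.46. Subtracting controls doubles the variance of each group's estimate, so the interaction has λ = 2.5 on 2 and 54 degrees of freedom and power 0.26. For gaps of 0.8 and 1.5 SD, power falls from 0.31 to 0.18 and from 0.82 to 0.53.

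**The case against.** The main efficacy claim, hypothesis 1, does use the randomised controls and is described only as preliminary evidence. The 3 x 2 x 2 model already contains the three-way term for the primary outcomes, and an article need not list every interaction. This limits the seriousness but does not remove the point: the article does not leave the test open. It names a within-arm ANOVA and a decision rule for these two hypotheses.

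Four stronger readings are tempting and are not supported.

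- A reader might infer that group differences in retest gain *will* appear as training effects. The documents give no such difference, and one in the other direction would hide an effect. This is a risk, not a demonstrated bias.
- A reader might take the omnibus rates as rates of false support for the hypothesis. The plan goes on to Bonferroni pairs, and support for hearing aid users above both other groups is much rarer.
- A reader might add regression to the mean, because hearing aid users may start lower. Groups are formed by age and audiometry, not by dual-task score, so each regresses towards its own mean. That mechanism is weak here.
- A reader might infer that the controls' HbO data are never used. The mixed models are planned for each outcome measure and may cover HbO. What can be said is that no comparison of arms is named as the test of hypothesis 3.

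Nor does the point extend to the statement that "correlations between dual-task performance and HbO levels will be conducted at baseline and after 12 weeks". The article does not say whether those correlations combine groups or arms.

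The low power of the interaction is a fair objection. It argues for estimates with intervals, not for a test that answers a different question.

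**Conclusion.** The point holds. As written, hypotheses 2 and 3 are judged by a comparison of non-randomised groups that cannot distinguish a larger training effect from a larger retest gain or drift.

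That confounding follows from the design of the test and needs no numerical assumption. Its size does. Under equal SDs and equally spaced gains at 10 per cell, omnibus false-positive rates run from about 7% to 46% for gaps of 0.25 to 1.0 SD, and false support for the hearing aid group exceeding both others from about 0.5% to 7%. If retest gain and drift are equal across groups, the planned test keeps its 5% level.

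**What to change.** Name the Age/Hearing Group x Training Group x Time interaction, in all randomised participants, as the test of hypothesis 2. Report the trained-minus-control difference in change for each age/hearing group, and the differences between groups, with confidence intervals. Fit the same model to HbO and name its interaction as the test of hypothesis 3. Keep the within-arm one-way ANOVAs as descriptive only.

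This changes the analysis wording and needs no extra participants or visits. Data Availability says recruitment is still ongoing, so the change can be recorded before the analysis. The cost is nominal power: about 0.26 instead of 0.46 for a 1.0 SD gap at 10 per cell. Hypotheses 2 and 3 should therefore be labelled exploratory and read from their estimates and intervals; a non-significant interaction should not be taken as evidence that training works equally well in all groups.
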